#### Data management {26}

Data entry: All data will be entered electronically into REDCap using standardized forms covering sociodemographic, clinical data, monitoring parameters, perceived exertion and questionnaires.Coding: Participants will be identified by randomly generated codes to ensure anonymity; no personally identifiable information will be linked to analytic datasets.Security: Access will be restricted to authorized researchers with role-based permissions; data will be encrypted within REDCap.Archiving: After completion, data will be archived for at least 5 years per ethical/regulatory guidance, with restricted access.Quality assurance: Range checks and consistency reviews will be applied; all data collectors will receive training to ensure standardized, reliable measurements.

### Confidentiality {33}

Collection of personal information: Personal and clinical data (e.g. sociodemographic, medical history, medications, exam results) will be collected solely for research purposes with participant authorization via written informed consent.

#### Protection of confidentiality

De-identification: Participants will be identified by unique codes; personally identifiable information will be stored separately from study data.Secure storage: Data will be stored on secure platforms (e.g. REDCap) with end-to-end encryption; access will be limited to authorized team members and to the minimum necessary.Restricted access: Password-protected accounts will limit data viewing to those involved in collection/analysis.Sharing: Information will be used exclusively for study purposes and will not be shared with third parties without prior consent. Any required sharing (e.g. for auditing) will occur only in aggregate and de-identified form.Post-study: Data will be securely maintained for a minimum of 5 years; access will remain restricted; secure disposal will follow expiration of the retention period.Participant assurances: All procedures will be explained in the informed consent, and participants may request deletion of their personal information as allowed by ethical regulations.

### Statistical methods

#### Statistical methods for primary and secondary outcomes {27a}

Analyses will be performed using SPSS Statistics v25.0 with significance level α = 0.05 (two-tailed). Primary outcome (total exercise duration) will be compared between groups using independent-samples *t* test, or Mann–Whitney *U* test if normality is violated (Shapiro–Wilk *p* < 0.05). Secondary outcomes will be compared using appropriate parametric or non-parametric tests. Likert-scale items will be analyzed using Mann–Whitney *U* tests. Descriptive statistics (means ± SD, medians [IQR]) will characterize all outcomes.

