#### Secondary outcomes

Exercise time and clinical parameters (systolic/diastolic blood pressure, respiratory rate, peripheral oxygen saturation, heart rate and rating of perceived exertion) during cycle-ergometer exercise with and without VR. These parameters will be measured across the exercise session, comparing the two approaches.Usability of the VR system during exercise, assessed using the System Usability Scale (SUS) [11, 12] administered after the session (intervention group): ease of use, comfort and perceived immersion.Patient satisfaction with the exercise experience, comparing sessions with and without VR, measured using the Physical Activity Enjoyment Scale (PACES) [13, 14].

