**BASELINE ASSESSMENTS (e)**				
Demographics and clinical history		X		
HADS (d)		X		
Baseline vital signs (BP, HR, SpO₂, RR)		X		
Modified Borg Scale (RPE)				
Baseline 12-lead ECG		X		

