### Sample size {19}

The sample size was estimated for adult inpatients with clinical HF decompensation who are hemodynamically stable and meet the study’s eligibility criteria. This is a prospective, randomized trial with a total sample of 60 participants (30 per group, control and intervention), defined by computer-generated 1:1 with no stratified.

Calculations were performed in G*Power (v3.1.9.2) assuming a superiority design with an independent-samples *t* test as the primary analysis. Based on prior VR exercise studies [11, 17, 26], we assumed a moderate effect size (Cohen’s *d* = 0.65) for the primary outcome (total exercise duration completed). With alpha set at 0.05 (two-tailed), beta at 0.20 (80% power) and assuming 10% dropout, the required sample size was determined to be 30 participants per group (*n* = 60 total). Secondary per-protocol analysis will include participants who completed the entire exercise session without unplanned termination.

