### Data collection and management

#### Plans for assessment and collection of outcomes {25a}

Data will be collected by trained physiotherapist who will supervise all exercise sessions and record data using standardized case report forms (CRF). Patient-reported satisfaction with the exercise experience will be assessed using the Physical Activity Enjoyment Scale (PACES) [18, 19], a 18-item self-report questionnaire administered immediately post-exercise to both groups. For the VR intervention group, system usability will be assessed using the System Usability Scale (SUS) [20, 21], a 10-item questionnaire administered immediately post-exercise to measure ease of use, comfort and perceived immersion with the VR technology.

Vital signs monitoring will be performed before, during (every minute) and after exercise using standardized equipment: pulse oximetry for oxygen saturation (SpO₂), automated sphygmomanometer for systolic and diastolic blood pressure (BP) and continuous heart rate monitoring via pulse oximeter and ECG. Continuous 12-lead ECG monitoring via bedside cardiac monitor will be performed during all exercise sessions for safety surveillance. Continuous ECG waveforms during the exercise session will not be archived. Only ECG strips corresponding to detected clinically significant arrhythmias (atrial fibrillation, ≥ 6 consecutive ventricular ectopic beats, sustained ventricular tachycardia** > **3 beats) or ischemic changes (≥ 1 mm ST-segment deviation from baseline) will be saved for post-hoc review by a blinded cardiologist.

Perceived exertion will be assessed using the Modified Borg Rating of Perceived Exertion Scale (0–10), administered at baseline, every minute during exercise and post-exercise to monitor exercise intensity and participant tolerance. All outcome data will be recorded in real-time on standardized forms during the exercise session to minimize measurement error and recall bias. Post-exercise questionnaires (PACES and SUS) will be administered while participant experience remains fresh, typically 5–10 min after exercise completion. All data will be entered into the secure REDCap database with mandatory quality checks for completeness, consistency and integrity before database lock.

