#### Methods for additional analyses (e.g. subgroup analyses) {27d}

Pre-specified subgroup analyses will examine potential treatment effect modifications by age, sex, LVEF and NYHA functional class. Subgroup-by-treatment interactions will be tested using linear regression with group-by-variable interaction terms. The significance threshold for interactions is α = 0.10 (exploratory). Results should be interpreted cautiously given potential for Type I error. Multivariable linear regression models will be used to adjust outcomes and control for potential confounders in secondary analyses.

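### The main comparison of physiological responses is not stated to use the pre-exercise values already collected, so it gives up precision it could have at no cost

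*Protocol article*

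**What the plan says.** Comparing physiological responses between groups is a secondary objective (Objectives {10}). Outcomes {16} lists systolic and diastolic pressure, respiratory rate, oxygen saturation, heart rate and perceived exertion as secondary outcomes and adds: "These parameters will be measured across the exercise session, comparing the two approaches".

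Pre-exercise values are collected. The participant timeline {18} marks the row "Baseline vital signs (BP, HR, SpO₂, RR" at time 0, and section {25a} says: "Vital signs monitoring will be performed before, during (every minute) and after exercise using standardized equipment". For perceived exertion, section {25a} says the scale is "administered at baseline, every minute during exercise and post-exercise to monitor exercise intensity and participant tolerance", but its row under baseline assessments in the timeline carries no mark.

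On analysis, section {27a} gives the primary outcome an independent-samples t test or Mann–Whitney test, then says: "Secondary outcomes will be compared using appropriate parametric or non-parametric tests". Mann–Whitney is named again for Likert items. Section {27d}, on additional analyses, says: "Multivariable linear regression models will be used to adjust outcomes and control for potential confounders in secondary analyses". It lists no covariates.

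**The concern.** The primary outcome, exercise time, has no baseline, so a two-group comparison of it is natural. The vital signs do have one. The objective concerns the response to exercise, and a comparison of exercise values alone mixes response with resting level. Section {27a} puts the secondary outcomes directly after the t test and Mann–Whitney pair, and regression adjustment appears only later, aimed at confounders. A reader would therefore take the main comparison to be unadjusted.

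With 30 per arm, no stratification ({21b}) and NYHA classes I to IV eligible ({14a}), the arms may differ at rest by chance. At stake is how well the trial can say whether VR changes haemodynamic load. An unadjusted result has a wider interval than necessary, and in a particular trial part of an apparent VR difference may be a resting difference.

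**Working it through.** **Inputs.** From the protocol: 30 per group, two-sided α = 0.05, unstratified 1:1 allocation. Assumed: a correlation ρ between baseline and exercise value of 0.3, 0.5 or 0.7, because the protocol gives none. The only effect size in the protocol is d = 0.65, set for exercise time. It is borrowed below purely as a yardstick, since no power is claimed for the vital signs.

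**The plan's own figure.** Section {19} derives 30 per group from d = 0.65 and "With alpha set at 0.05 (two-tailed), beta at 0.20 (80% power) and assuming 10% dropout". The exact two-sided t calculation needs 39 per group before dropout and 39/0.90 = 43.3, so 44, after it. At 30 per group the two-sided power is 69.7%. The stated 30 is reproduced only by a one-sided test without dropout (power 80.0%). That is a separate matter, and the present point does not depend on it.

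**Step 1: chance baseline difference.** In SD units, the difference in baseline means has standard deviation √(2/30) = 0.258. Its 95% range is ±1.96 × 0.258 = ±0.51. The probability that it exceeds 0.25 SD in either direction is 0.33, and that it exceeds 0.5 SD is 0.05.

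**Step 2: carry-over.** The expected shift in the unadjusted contrast is ρ times the baseline difference.
- One standard deviation of imbalance (0.258): 0.08, 0.13 and 0.18 SD for ρ = 0.3, 0.5 and 0.7.
- Edge of the 95% range (0.506): 0.15, 0.25 and 0.35 SD.

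**Step 3: precision.** Relative to a comparison of exercise values alone, baseline adjustment multiplies the variance by 1 − ρ². Unadjusted, the smallest difference detectable with 80% power is (1.96 + 0.84) × 0.258 = 0.72 SD. Adjusted, it is that figure times √(1 − ρ²). Power for 0.65 SD comes from the noncentral t with noncentrality 0.65 × √15 / √(1 − ρ²), losing one degree of freedom for the covariate.

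| ρ (assumed) | Variance factor | Variance saved | 30 per arm is worth, unadjusted | Detectable difference | Power for 0.65 SD |
|---|---|---|---|---|---|
| No adjustment | 1.00 | – | 30 | 0.72 SD | 69.7% |
| 0.3 | 0.91 | 9% | 30/0.91 = 33 | 0.69 SD | 73.7% |
| 0.5 | 0.75 | 25% | 30/0.75 = 40 | 0.63 SD | 81.5% |
| 0.7 | 0.51 | 49% | 30/0.51 = 59 | 0.52 SD | 93.4% |

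In simulation (20,000 trials, 30 per arm) the variance ratios were 0.77 at ρ = 0.5 and 0.53 at ρ = 0.7. These are slightly less favourable than the formula because the slope has to be estimated.

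**Step 4: validity of the unadjusted test.** In the same simulation its mean shift was about zero and its type I error was 0.051 (ρ = 0.5) and 0.049 (ρ = 0.7). Among trials where one arm's baseline mean exceeded the other's by more than 0.5 SD, its error was about 0.20 and 0.29. Such trials are uncommon, and the overall 5% already averages over them.

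**The case against.** The strongest reply is that section {27a} names no test, summary or time point for the vital signs. Analysis of covariance is a parametric method and fits the sentence. Section {27d} promises regression that adjusts outcomes and excludes no covariate, and an analysis plan not shown may give the detail. This stands against one tempting inference, that the protocol prescribes two-sample tests or decides to disregard baseline values. It does neither. What remains is that the one place that sets the method for these outcomes does not commit to the baseline, and that adjustment is placed among additional analyses. Using a value already collected is a better method, not merely a request for detail.

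A second tempting inference is that chance imbalance makes the comparison biased or inflates false positives. Step 4 shows that it does not, taken over all randomisations. The loss is precision, together with harder interpretation of a trial that happens to be imbalanced.

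Three further objections also stand. The size of the gain depends on an assumed correlation and is modest at 0.3. Resting perceived exertion may sit near the floor of its scale (an assumption), so its baseline may help little even if taken. And the VR arm has a familiarisation period that includes 30 to 60 seconds of pedalling ({15a}), so a reading taken just before the exercise blocks could already reflect allocation. Adjusting for such a reading could itself introduce bias.

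**Conclusion.** The point holds as a matter of precision. For heart rate, systolic and diastolic pressure, respiratory rate and oxygen saturation, the main between-group comparison is not stated to use the baseline values the trial collects. If it is run unadjusted, it forgoes a variance reduction of about 9%, 25% or 49% at correlations of 0.3, 0.5 or 0.7, and it leaves a chance resting difference (standard deviation 0.26 SD units) in the contrast. These figures rest on 30 analysed per arm, a linear relation and the assumed correlations. The power figures also borrow the primary outcome's effect size. The unadjusted test would still be valid, and the primary outcome is unaffected. The change is worth making because it is free, not because the result would otherwise be wrong.

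**What to change.** In section {27a}, state that for heart rate, systolic and diastolic pressure, respiratory rate and oxygen saturation the main between-group comparison is a linear model, or a mixed model for the minute-by-minute values, with group and the participant's own baseline value of that variable as covariate. Report the adjusted mean difference with its 95% CI. Define baseline as the value measured before randomisation and before VR familiarisation. Section {23} already places randomisation after the baseline assessments, so this value should exist.

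Reconcile the timeline {18} with section {25a} on whether perceived exertion is taken at baseline, and include it in the model only if it is. Keep the existing tests for PACES, which has no baseline.

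The cost is a sentence or two and a correction to the schedule, with no extra participants or procedures. SPSS, already the named software, fits these models. Since sessions can stop early, the text should also say which time points enter the model; baseline adjustment does not settle that. The wording should be fixed before outcome data are analysed, so that raw values, change scores and adjusted models are not chosen between afterwards. If an analysis plan already specifies this, section {27a} need only be aligned with it.

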#### Who will be included in each analysis {27b}

All randomized participants who provided informed consent and were allocated to a group will be included in the primary intention-to-treat (ITT) analysis, according to their original allocation, regardless of adherence or protocol deviations. Secondary per-protocol analysis will include participants who completed the entire planned exercise session without unplanned termination due to participant request or safety concern. Analysis will be based on actual exercise duration achieved by each participant (measured continuously, independent of exercise structure). Results from per-protocol analysis will be compared with intention-to-treat findings to assess robustness of primary findings.

#### How missing data will be handled in the analysis {27c}

For primary and secondary outcomes, every effort will be made to minimize missing data through robust follow-up and documentation procedures during the single-session design. If missing data occur for the primary outcome, a complete-case analysis will be performed. As a sensitivity analysis, multiple imputation will be considered if the proportion of missing data exceeds 5%. Missing data patterns and reasons will be described in detail. All analyses involving missing data will be clearly reported, and no participants will be excluded solely due to missing data for secondary or exploratory outcomes.

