##### VR familiarization

Headset fitting and display adjustment (~ 1 min): Proper fit, comfort verification, interpupillary distance (IPD) calibration, head strap tensionOrientation to virtual environment (~ 2 min): Participant views VR environment while stationary; guided tour of the virtual settingMovement practice (~ 30–60 s): Participant pedals at low intensity while observing synchronized avatar movementComfort and safety assessment: Supervising physiotherapist assesses for any discomfort, dizziness or nausea; session proceeds only if participant comfortableSafety procedures reviewed: Emergency exit procedures, communication methods and participant controls explained

Participants experiencing significant discomfort during familiarization will not proceed to the exercise protocol.

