**POST-EXERCISE ASSESSMENTS**				
Total exercise time (minutes) (g)				X
Recovery vital signs				X
SUS—VR group only (i)				X
PACES (h)				X
Adverse events assessment (j,k)				X

a) Single-session design: Only ONE exercise session per participant during hospitalization.

b) Timepoints: Enrollment → Randomization → Intervention → Post-Exercise/Close-Out. No follow-up.

c) Both groups identical protocol except: VR group receives immersive VR headset; control group receives standard cycle ergometer.

d) Hospital Anxiety and Depression Scale (HADS): 14-item self-report questionnaire assessing anxiety (7 items, score 0–21) and depression (7 items, score 0–21) during acute hospitalization [24, 25]

e) Continuous vital signs monitoring: Blood pressure (BP, mmHg, systolic/diastolic), heart rate (HR, bpm), peripheral oxygen saturation (SpO₂, %) and respiratory rate (RR, breaths/min) recorded every minute throughout exercise and recovery period via automated monitors and continuous 12-lead ECG.

f) Session termination criteria: Immediate termination triggered if Rating of Perceived Exertion (RPE) ≥ 5 (‘hard’ intensity) OR if any safety threshold exceeded: BP > 200 mmHg or < 80 mmHg (systolic), HR > 130 or < 40 bpm,SpO₂ < 85% or ST-segment changes on ECG.

g) Total exercise time: Cumulative pedaling time (minutes) from initiation to termination.

h) Physical Activity Enjoyment Scale (PACES): 18-item questionnaire (score 18–80); higher = greater enjoyment [18, 19]

i) System Usability Scale (SUS10-item questionnaire (score 0–100); ≥ 68 indicates above-average usability; ≥ 70 considered acceptable for clinical implementation [20, 21]

j) Adverse events: Serious (requiring intervention) vs. non-serious. Documented immediately post-exercise.

k) Real-time data collection: All vital signs, RPE, observations recorded by physiotherapist on paper CRF during exercise; transferred to REDCap same day.

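### The only sensitivity analysis for missing exercise times is an optional imputation above 5% missing, which cannot test loss related to the participant's own exercise tolerance

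*Protocol article*

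**What the plan says.** Section {27c} (missing data) fixes the main approach: "If missing data occur for the primary outcome, a complete-case analysis will be performed". It then names one further analysis: "As a sensitivity analysis, multiple imputation will be considered if the proportion of missing data exceeds 5" per cent. The threshold is not given by arm, so I read it as applying to the whole trial.

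Section {27b} (who will be included) defines the primary set: "All randomized participants who provided informed consent and were allocated to a group will be included in the primary intention-to-treat (ITT) analysis", "regardless of adherence or protocol deviations". It adds a per-protocol analysis of people who finished the session: "Results from per-protocol analysis will be compared with intention-to-treat findings to assess robustness of primary findings".

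The sample size section {19} sets 30 per group, "assuming 10% dropout".

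Two design features matter. The footnotes to the participant timeline {18} say: "Single-session design: Only ONE exercise session per participant during hospitalization". The VR familiarization section says: "Participants experiencing significant discomfort during familiarization will not proceed to the exercise protocol". Only the intervention arm has that step, and the article does not say whether such a participant has a missing exercise time or a time of 0 min.

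**The concern.** A sensitivity analysis is useful when it relaxes the assumption most likely to fail. Here the assumption most at risk is that people with no exercise time would have exercised as long as similar people who have one. Someone who is unwell in the headset, deteriorates, or declines to start may well have had a short session. The familiarization step allows such loss in the VR arm alone.

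Standard imputation fills those gaps from participants who did exercise, so it keeps that assumption, conditional on baseline data. Below the trigger even that check is absent, and above it the check is optional. The per-protocol comparison does not help: it keeps only people who completed the session, so it says nothing about those with no value. If loss is related to tolerance and falls mainly on the VR arm, the complete-case difference favours VR and no planned analysis would test how far.

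**Working it through.** **Inputs from the article.** 30 per arm, 60 in total; d = 0.65; two-sided α = 0.05; 10% dropout; unadjusted t test, or Mann–Whitney U if normality fails; complete cases; 5% trigger. (The stated d, α and power give 39 per group by the t test, and 39/0.9 → 44 with dropout, rather than 30. That is a separate matter; the planned 30 is used here.)

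**Assumptions, not in the article.** SD of exercise time 3 to 4 min; VR mean 10 to 12 min.

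**1. The trigger.** 5% of 60 = 3. Three missing values are 3/60 = 5.0%, which does not exceed 5%, so the rule starts at 4. Three losses in one arm are 3/30 = 10% of that arm. The planned 10% dropout is 6 of 60.

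**2. What imputation can and cannot correct.** Simulation: 30 per arm, true difference 0.65 SD, six values missing in the VR arm, 400 replicates, 50 normal-model imputations, one baseline covariate with correlation r to the outcome. The six lost were those with the lowest covariate (first block) or the lowest outcome (second block), after adding noise of SD 0.5. Mean differences in SD units:

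| Loss depends on | r | Full data | Complete case | MI, arm only | MI, arm + covariate |
|---|---|---|---|---|---|
| covariate | 0.3 | 0.659 | 0.750 | 0.751 | 0.659 |
| covariate | 0.5 | 0.657 | 0.808 | 0.809 | 0.656 |
| covariate | 0.7 | 0.626 | 0.841 | 0.842 | 0.627 |
| outcome | 0 | 0.626 | 0.924 | 0.924 | 0.923 |
| outcome | 0.3 | 0.663 | 0.967 | 0.967 | 0.943 |
| outcome | 0.5 | 0.640 | 0.937 | 0.938 | 0.870 |
| outcome | 0.7 | 0.659 | 0.962 | 0.963 | 0.825 |

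With covariate-driven loss, imputation using that covariate recovers the full-data value. With outcome-driven loss, the share of bias left is (MI − full)/(complete case − full): 0.297/0.298 = 100% at r = 0, 0.280/0.304 = 92% at 0.3, 0.230/0.297 = 77% at 0.5 and 0.166/0.303 = 55% at 0.7.

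**3. An extreme not-at-random scenario.** If k VR values are missing and scored 0 min, the difference falls from D to D − (k/30) × VR mean. With an assumed mean of 11 min the shift is 11k/30: 0.73, 1.10 and 2.20 min for k = 2, 3 and 6. At an assumed SD of 4 min, the planned effect is 0.65 × 4 = 2.6 min.

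Worked case (mean 10, SD 4, k = 3, observed D = 2.6):
- Complete case: SE = √(16/27 + 16/30) = 1.061; t = 2.45 on 55 df; p = 0.017.
- Zero-scored: VR mean = 27 × 10/30 = 9. VR variance = (26 × 16 + 27 × 1² + 3 × 9²)/29 = 23.66. Difference = 9 − 7.4 = 1.6; SE = √(23.66/30 + 16/30) = 1.150; t = 1.39 on 58 df; p = 0.169.

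Over means of 10 and 12 min and SDs of 3 and 4 min (complete-case difference 1.95 or 2.60 min):

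| k missing, all VR | Complete-case p | Zero-scored difference (min) | Zero-scored p |
|---|---|---|---|
| 2 | 0.016 | 1.15 to 1.93 | 0.088 to 0.227 |
| 3 | 0.017 | 0.75 to 1.60 | 0.169 to 0.460 |
| 4 | 0.019 | 0.35 to 1.27 | 0.287 to 0.743 |
| 6 | 0.021 | −0.45 to 0.60 | 0.627 to 0.962 |

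**4. Balanced loss.** With three missing per arm, all scored 0, the difference becomes D × 27/30: 2.6 falls to 2.34 min. The large shifts need one-sided loss.

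**The case against.** A reader might infer that, with one session and no earlier outcome value, imputation has nothing to work with and must return the complete-case answer. The documents do not support that. The primary test is unadjusted, so complete-case analysis needs missingness within an arm to be unrelated to the outcome. Imputation with baseline data needs less, and the article collects age, sex, LVEF, NYHA class and HADS before the session. The first block of the simulation shows imputation moving the estimate, and moving it correctly. It matches complete case only when the model holds arm alone or uninformative covariates, or when loss is unrelated to them.

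Other points on that side:
- The minute shifts put every loss in the VR arm and score every loss as 0. The 10% allowance is for the trial overall, and someone who leaves for an unrelated reason has not shown zero tolerance. This stands: the figures are bounds, not forecasts.
- Section {27c} undertakes to describe missing-data patterns and reasons, so one-sided loss would be visible to readers. This stands, but seeing the loss does not show whether the conclusion survives it.
- If familiarization stops are scored 0 min, they are not missing at all. True, and the article does not settle it.
- The imputation model and further sensitivity analyses may sit in an analysis plan that is not shown. Their absence is therefore no fault. The point rests on the rule that the article does state: one optional analysis, its threshold, and the assumption it usually carries.

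**Conclusion.** The point holds in a limited form. The one stated missing-data check can correct loss explained by measured baseline factors but cannot test loss tied to exercise tolerance. The 5% trigger leaves up to three losses, possibly 10% of one arm, without any check. In the simulated outcome-driven loss, 55% to 100% of the bias remained after imputation; that selection was strong, so the share illustrates the limit and predicts nothing. The shifts of 0.7, 1.1 and 2.2 min rest on an assumed 11-min mean, loss in the VR arm only, and scores of 0.

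It would go too far to conclude that imputation is worthless here, or that a false VR benefit is bound to be reported as robust: the baseline data and the reporting commitment in {27c} argue against both. The primary analysis need not change on this ground. This is a cheap improvement.

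**What to change.** In {27c}, or in the analysis plan:

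1. Remove the 5% trigger.
2. Keep multiple imputation as a secondary check, with arm and the collected baseline covariates (age, sex, LVEF, NYHA class, HADS) in the model.
3. Whenever any primary value is missing, add a tipping-point analysis that shifts the imputed times by a separate delta in each arm. Include missing values set to 0 min as one scenario, labelled extreme. State whether the conclusion changes, and at what delta.
4. State whether participants stopped at familiarization count as missing or as 0 min. Do this before database lock, and so before unblinding. Only one arm has that step, so deciding later could reveal which coded group is VR.

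The cost is a few sentences and a few more analysis lines on 60 records. If the change is treated as a substantial change to the analyses, the protocol amendments section {31} also requires ethics approval and a registry update. The bounds will look wider than the imputed result; that width is the uncertainty that the present rule does not show.
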